## Abstract

**Introduction:**

The potential for telehealth-based interventions to provide remote support, education and improve self-management for long-term conditions is increasingly recognised. This trial aims to determine whether an intervention delivered through an easy-to-use tablet computer can improve the quality of life of patients with chronic obstructive pulmonary disease (COPD) by providing personalised self-management information and education.

**Methods and analysis:**

The EDGE (sElf management anD support proGrammE) for COPD is a multicentre, randomised controlled trial designed to assess the efficacy of an Internet-linked tablet computer-based intervention (the EDGE platform) in improving quality of life in patients with moderate to very severe COPD compared with usual care. Eligible patients are randomly allocated to receive the tablet computer-based intervention or usual care in a 2:1 ratio using a web-based randomisation system. Participants are recruited from respiratory outpatient clinics and pulmonary rehabilitation courses as well as from those recently discharged from hospital with a COPD-related admission and from primary care clinics. Participants allocated to the tablet computer-based intervention complete a daily symptom diary and record clinical symptoms using a Bluetooth-linked pulse oximeter. Participants allocated to receive usual care are provided with all the information given to those allocated to the intervention but without the use of the tablet computer or the facility to monitor their symptoms or physiological variables. The primary outcome of quality of life is measured using the St George's Respiratory Questionnaire for COPD patients (SGRQ-C) baseline, 6 and 12 months. Secondary outcome measures are recorded at these intervals in addition to 3 months.

**Ethics and dissemination:**

The Research Ethics Committee for Berkshire—South Central has provided ethical approval for the conduct of the study in the recruiting regions. The results of the study will be disseminated through peer review publications and conference presentations.

**Trial registration:**

Current controlled trials ISRCTN40367841.

Strengths and limitations of this studyThe study focusses on the impact of a self-management intervention delivered through a low-cost Internet enabled tablet computer.The study is powered to examine quality of life outcomes and uses an unbalanced allocation to examine the effect of the EDGE (sElf management anD support programme) platform across a wide range of participants.The study is not sufficiently large enough to provide a detailed cost-effectiveness evaluation, or to provide sufficient power to demonstrate clinically important differences between intervention and usual care groups for hospital admission rates.

## Background

Chronic obstructive pulmonary disease (COPD) is an important cause of morbidity and mortality worldwide responsible for three million deaths globally per year.^1^ In the UK, the total annual estimated cost of COPD to the National Health Service (NHS) is over £800 million, with over half of this attributable to hospital-based care,^2^ and the impact of COPD to the health-related quality of life of patients is well established.^3^
^4^ There is now promising evidence that training and support for patients in the self-management of their condition improves quality of life and can reduce unplanned hospital admissions.^5^
^6^ However, the results of individual studies are mixed,^7^ and the challenge remains to identify those for whom different forms of self-management are suitable and to develop and optimise ways of delivering available interventions to maximise effectiveness and safety.

Use of the converging computer and communication technologies in the form of telehealth-based interventions offers a means of helping patients monitor their condition, providing support in interpreting data, providing a means of delivering individually tailored education and treatment plans and allowing clinicians to monitor long-term trends and identify short-term safety issues.

Evaluation of telehealth-based interventions can be complex with a requirement for considering multiple perspectives within the evaluation.^8^ For a successful evaluation, there is a need to improve the delivery of clinical care, control the workload placed on healthcare professionals and to provide cost-effective improvements in treatment outcomes.

Systematic reviews of telehealth in COPD provide evidence to support continuing research,^9^ but recent large-scale evaluations of telehealth-based treatment programmes have not shown convincing evidence of effectiveness.^10^
^11^ The challenge remains to ensure that the telehealth systems can be easily used by patients and that the systems integrated into the healthcare system are acceptable to clinicians and patients. Criticism of previous systems has included difficulty with data entry, leading to lifestyle restriction, unreliability of monitoring devices and lack of integration within an individual patient's day-to-day life.

Our group has long experience of developing and testing healthcare interventions based on the use of mobile phones and their integration into clinical care delivery. Mobile phones or tablet computers with a subscriber identity module (SIM) card provide a platform in which communication and computing technologies are sustainably integrated and a platform for communicating with monitoring devices. We have recently carried out a cohort study in which we have shown that a tablet-computer based system for supporting patients with COPD is acceptable and feasible.^12^

We have therefore set out to determine the efficacy of an Internet-linked tablet computer-based intervention (the EDGE—sElf management anD support proGrammE—platform), with patients with moderate to very severe COPD, in improving quality of life measured with the St Georges Respiratory Questionnaire for COPD patients (SGRQ-C) in comparison with standardised usual care. In addition, we will collect data on morbidity, mortality and hospital admissions to inform the design of future evaluations of the system.

## Methods

### Trial design

The EDGE for COPD is a multicentre, randomised controlled trial of 12-month duration. Patients are individually randomised to receive either an Internet-linked tablet computer (the EDGE platform)-based intervention or standardised usual care in a 2:1 allocation ratio (figure 1).

**Figure 1 BMJOPEN2013004437F1:**
[figure not shown]
Patient flow. EDGE, sElf management anD support programme; SGRQ-C, St George's Respiratory Questionnaire for COPD patients.

### Participants

#### Eligibility criteria for participants

Eligible patients are those aged ≥40 years with a confirmed diagnosis of COPD defined as a forced expiratory volume in one second (FEV_1_), post-bronchodilation of <80% and a predicted ratio of FEV_1_ to forced vital capacity of <0.70. Eligible patients have a smoking-pack history >10 pack-years and a Medical Research Council dyspnoea score ≥2. A clinical decision of trial suitability for patients who are unable, for clinical reasons, to provide a spirometry reading at full assessment is sufficient for eligibility if the patient has prior clinical evidence of COPD (eg, obstructive spirometry within the past 10 years or radiological evidence of emphysema). Patients are required to be registered with a general practitioner and have had an exacerbation of COPD requiring home treatment or hospital admission in the previous year or have been referred for pulmonary rehabilitation.

Patients are not eligible for trial participation if they have other significant lung disease or chronic heart failure (defined by the New York Heart Association classification system as severe (grade IV)) or a life expectancy of <3 months. Eligible patients must be able to provide informed consent, to complete the trial questionnaires and not be cognitively impaired. Patients living in areas without access to an Internet-enabled mobile phone network and thus unable to transmit and receive data are not eligible to enter the trial.

#### Setting

To maximise recruitment of participants to the trial, patients are identified from a variety of settings encompassing primary and secondary care as well as community services. Patients attending respiratory hospital outpatient clinics and pulmonary rehabilitation courses in the adjacent counties of Oxfordshire and Berkshire, UK, are invited to participate. In addition, eligible patients are identified from primary care clinics and from those recently (within the preceding 2 weeks) discharged from hospital following a COPD-related admission.

### Trial interventions

#### Intervention development and specification

We developed and tested an intervention to support patients with COPD in monitoring their health and to provide information and education about their condition based on use of an Internet-linked tablet computer (the EDGE platform). Based on open architecture application software, the EDGE platform was developed to allow integration within clinical care by a team of clinicians and engineers working with patients. The platform was refined in a 6-month cohort study with a group of patients with COPD selected using eligibility criteria matching those of the trial. Key principles underlying the development of the platform include ease of use for a group of participants less experienced with computers (large icons, no keyboard needed for data entry) and ensuring data quality (tablet-based instructions to ensure ease of use, development of algorithms to assure data quality).

The EDGE platform intervention incorporates a daily symptom diary consisting of a series of standard questions about symptoms based on previous trial protocols.^2^
^13^
^14^ Questions include general well-being, cough, breathlessness, sputum (quantity produced and colour) and use of medications. A 30 second period of data transmission using a Bluetooth-enabled pulse oximeter with finger probe allows daily collection of pulse rate and oxygen saturation data. Every 4 weeks, beginning 2 weeks after initial use, the platform presents the four-item Patient Health Questionnaire (PHQ-4) screening measure^5^
^15^ and if either the depression or anxiety components score is ≥3 then the relevant full questionnaire (depression (PHQ-8)^6^
^16^) or Generalised Anxiety Disorder 7-item (GAD-7^7^
^17^), is presented for completion.

The EDGE platform also includes software modules to provide patients with additional support for self-management of their condition. These include (1) personalised plans for self-management and treating an exacerbation of their condition; (2) brief video clips and text-based material providing additional information about COPD and treatments (including medicines use and inhaler technique), and educational advice on managing COPD, smoking cessation, diet, physical activity and mood management (depression and anxiety); and (3) the facility to receive a brief message from their respiratory nurse. Prompts for accessing the physical activity and mood management information are included for patients reporting higher scores on the depression and anxiety screening measures.

The data entered onto the EDGE platform is transmitted immediately to a server hosted behind NHS firewalls. The data held on the server is reviewed at no less than 4-day intervals by a clinician to identify technical problems and review clinical data received.

In an initial 6-week period of use, EDGE-platform users complete the symptom diary and record their oxygen saturation and heart rate with the pulse oximeter on a daily basis. Following this initial run-in period of use, the distributions of values for the oxygen saturation, heart rate and symptom scores are calculated for the run-in period for each participant. The 95th centile is computed for each distribution and used as the threshold for the participant's safety alert for that parameter. Every time the participant-specific threshold for a parameter is crossed after the run-in period, the safety alert is displayed on the web-based record for that participant.

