#### The EDGE platform-based intervention

Participants allocated to receive the Internet-linked tablet computer (EDGE platform)-based intervention are provided with an Android tablet computer (Samsung Galaxy Tab) running the application software and Bluetooth-enabled oximeter probe (Nonin, PureSAT, 956OBT, Nonin Medical Inc, Plymouth, Minnesota, USA). Participants are briefly instructed on the use of the EDGE platform by the research nurse and are provided with a brief information booklet giving details of its use. Participants continue to input their symptom data and clinical recordings daily throughout the duration of the trial. Patients are informed that the EDGE system is not a replacement for their usual clinical care, and that in the event of deterioration in their health they should contact their general practitioner or community respiratory nurse as usual. However, data are reviewed by a clinician at no less than 4-day intervals, and changes in heart rate, oxygen saturation or symptom score that cross the participant's specific threshold for that parameter and persist for more than 4 days are followed up with a phone call to either the patient, general practitioner or community respiratory nurse as appropriate. If depression or anxiety scores equal or exceed a threshold of 10, then the general practitioner is informed by letter.

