## Discussion

This trial is designed to assess the extent to which a telehealth platform designed to support self-management improves quality of life for people with COPD. Reduced quality of life is an important aspect of COPD that has been shown to be responsive to group and one-to-one interventions.^7^ This trial is powered to show a clinically important effect and provide data from which to design further trials to explore cost-effectiveness and potential reduction in hospital admissions.

The trial intervention uses a novel implementation of telehealth using a non-proprietary tablet computer designed to be integrated into day-to-day life and clinical care. In addition to being non-obtrusive, it provides, at relatively low cost, in relation to previous telehealth systems, facilities for monitoring, communication, self-management support and education delivery. The development of the system was carried out iteratively using best practice to involve patients, engineers and clinicians in repeated testing and assessment.^28^

The underlying approach in implementing telehealth within this trial is to provide a system focused around the needs of the patient with collection of data that can be analysed over a period of time and used to inform future management. Although future implementations of this system may allow real-time alerts to inform management, consistent experience to date with existing commercial telehealth systems has been that the high rates of false-positive alerts have been unacceptable to clinicians and patients. This trial will provide data to evaluate the potential of the patient-specific tailored alerts available in the system for implementation in practice.

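### The oxygen-saturation safety alert is set at the 95th centile of the run-in readings, the wrong tail for a measure that worsens by falling

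*Protocol article*

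**What the plan says.** In the protocol article, under Intervention development and specification, the platform collects daily readings over a six-week run-in. After that, "the distributions of values for the oxygen saturation, heart rate and symptom scores are calculated for the run-in period for each participant". One rule then covers all three parameters: "The 95th centile is computed for each distribution and used as the threshold for the" participant's safety alert. The trigger is given without a direction: "Every time the participant-specific threshold for a parameter is crossed after the run-in period, the safety alert is displayed" on the participant's web record.

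The next section, The EDGE platform-based intervention, attaches a clinical action to the same threshold. It concerns "changes in heart rate, oxygen saturation or symptom score that cross the participant's specific threshold for that parameter and persist for more than 4 days", and these lead to a phone call to the patient, the general practitioner or the community respiratory nurse.

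The Discussion gives the alerts a research purpose as well: "This trial will provide data to evaluate the potential of the patient-specific tailored alerts available in the system". It also reports that high false-positive rates in existing commercial systems have not been acceptable to clinicians or patients.

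**The concern.** For heart rate the upper tail is the adverse one. The same holds for the symptom score if a higher score is worse, which the article does not state and is assumed here. For oxygen saturation, deterioration in COPD is a fall, so its 95th centile describes good days. Neither section gives a 5th centile, a direction of crossing or a reversed scale for saturation.

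The alert and the phone call are part of the intervention under test, and saturation is one of the two physiological signals collected. If the software follows the text, either the alert misses desaturation or it is on almost permanently. If it does something else, the published description is not of the algorithm that was run. A reader could then neither replicate the alerts nor interpret the planned evaluation of them.

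**Working it through.** **No plan figure to reproduce.** No sample size, power or error rate depends on this rule. The check is how the stated rule behaves for saturation under each direction of crossing, compared with a lower-tail rule.

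**Inputs from the article.** 95th centile for each parameter; a six-week daily run-in, so 6 × 7 = 42 readings; a 12-month trial, so 365 − 42 = 323 later days; a call when the crossing lasts more than 4 days, so at least 5 consecutive days.

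**Assumed inputs.** The article gives no saturation data. Mean 92%; within-patient SD 1 to 3 points; normal readings, one every day; whole-percent or unrounded values; day-to-day correlation 0 or 0.5.

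**Step 1: exact result with known centiles.** Let saturation fall by *k* within-patient SDs. With Φ the standard normal distribution function:

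- P(above 95th centile) = 1 − Φ(1.645 + *k*)
- P(below 95th centile) = Φ(1.645 + *k*)
- P(below 5th centile) = Φ(−1.645 + *k*)

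| Fall *k* (SD) | Above 95th | Below 95th | Below 5th |
|---|---|---|---|
| 0 (stable) | 5.0% | 95.0% | 5.0% |
| 1 | 0.41% | 99.6% | 25.9% |
| 2 | 0.013% | 99.99% | 63.9% |

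The above-95th rule alerts less often as the patient worsens. The below-95th rule is saturated from the start and barely moves. Only the lower-tail rule is quiet in stability and rises with deterioration.

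**Step 2: thresholds estimated from 42 readings.** Results for whole-percent, independent readings, 4,000 simulated patients per setting, share of days:

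| SD | Fall (points) | Above 95th | Below 95th | Below 5th |
|---|---|---|---|---|
| 1.0 | 0 | 4.9% | 82.3% | 4.8% |
| 1.0 | 4 | 0.0% | 100.0% | 97.5% |
| 1.5 | 0 | 5.0% | 87.4% | 5.2% |
| 1.5 | 4 | 0.0% | 100.0% | 82.0% |
| 2.0 | 0 | 5.9% | 89.1% | 6.0% |
| 2.0 | 4 | 0.0% | 99.9% | 63.9% |

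Whole-percent rounding lowers the stable below-95th share, because a reading equal to the threshold does not count as below it.

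**Step 3: full range of settings.** With 10,000 patients per setting, SD 1, 1.5, 2 or 3, both correlations, rounded and unrounded:

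- Stable, below the 95th centile: 82–93% of days with independent readings and 81–92% with correlation 0.5. Below the 5th centile: 5–8% (0.048 to 0.081).
- Sustained 4-point fall, above the 95th centile: 0 to 0.4% of days. Below the 5th centile: 41–99%.

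**Step 4: the phone-call condition.** Over 323 stable days, runs of at least 5 consecutive days below the 95th centile number 12.4 to 18.4 per patient. Below the 5th centile there are 0.00 to 0.31.

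**The case against.** The strongest reply is that there is a third reading. The 95th centile may be shorthand for the most extreme 5% in the unsafe direction, which would suit something called a safety alert. Clinicians and engineers built the platform and refined it in a six-month cohort study of patients with COPD, and the Discussion shows awareness of false alerts. A rule that is on for over 80% of stable days, or silent during desaturation, fits poorly with that history. This is plausible and probably what was intended. It remains inference: nothing in the text says it, and the article does not report that the alerts themselves were tested in the cohort.

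A second reply is that a journal article leaves algorithm detail to fuller documents. That would excuse silence on the threshold. Here the article states a specific centile and applies it to every distribution, so the objection is to what is stated.

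Third, the simulation describes only the literal wording. That is right: it is no evidence about the deployed software. The 12 to 18 runs are occasions on which the persistence condition is met, not a forecast of calls, since a clinician reviews the data before calling.

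Fourth, if the raw readings are kept on the server, a lower-tail threshold can be applied afterwards and the alerts evaluated on that basis. This stands in part. It does not recover alerts that were missed or calls that were made under the wrong rule during the trial.

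**Conclusion.** The point holds. As written, the threshold is wrong for oxygen saturation whichever way crossing is read: past it on 81–93% of stable days, or an alert on at most 0.4% of days after a sustained 4-point fall. The exact percentages depend on the assumed mean, SD, rounding and correlation. The direction of the failure does not, because it follows from using the upper tail for a measure whose adverse direction is downward. That premise is general clinical knowledge and is not stated in the article.

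The consequence is limited. One of three parameters is affected, a clinician also looks at the incoming data, and patients are told to contact their usual services if they deteriorate. The sample size, randomisation and SGRQ-C analysis do not change. The point should still be fixed, because it concerns a safety function within the tested intervention and a rule that the trial means to evaluate. Whether the software has the same fault cannot be judged from the article.

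**What to change.** In Intervention development and specification, replace the single rule with two:

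- **Oxygen saturation:** threshold at the 5th centile of the participant's run-in readings, alert when a reading is below it.
- **Heart rate and symptom score:** threshold at the 95th centile, alert when a reading is above it (confirming that a higher symptom score is worse).

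Use the same directions in The EDGE platform-based intervention for the rule on crossings that "persist for more than 4 days are followed up with a phone call". Check the deployed algorithm against this wording. If it used the upper tail for saturation, correct it and record the date, so that alerts before and after can be separated in the planned evaluation.

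The cost is a sentence of text and one software check. No new data are needed, and neither the sample size nor the primary analysis changes.

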#### The EDGE platform-based intervention

Participants allocated to receive the Internet-linked tablet computer (EDGE platform)-based intervention are provided with an Android tablet computer (Samsung Galaxy Tab) running the application software and Bluetooth-enabled oximeter probe (Nonin, PureSAT, 956OBT, Nonin Medical Inc, Plymouth, Minnesota, USA). Participants are briefly instructed on the use of the EDGE platform by the research nurse and are provided with a brief information booklet giving details of its use. Participants continue to input their symptom data and clinical recordings daily throughout the duration of the trial. Patients are informed that the EDGE system is not a replacement for their usual clinical care, and that in the event of deterioration in their health they should contact their general practitioner or community respiratory nurse as usual. However, data are reviewed by a clinician at no less than 4-day intervals, and changes in heart rate, oxygen saturation or symptom score that cross the participant's specific threshold for that parameter and persist for more than 4 days are followed up with a phone call to either the patient, general practitioner or community respiratory nurse as appropriate. If depression or anxiety scores equal or exceed a threshold of 10, then the general practitioner is informed by letter.

